### Statistical analysis

We analyse data on an intention-to-screen basis. We evaluate the outcomes of the intervention on a patient level.

### Primary study outcomes

The difference in yield of new AF in 1 year between intervention and control practices is estimated by calculating the difference in detection rate of new AF (new cases of AF after 1 year within the clusters/all patients in the clusters) between intervention and control practices. We use logistic mixed-effects models with practice as random factor for statistical analysis, since this accounts for the correlation between patients within the same practice. In case the outcome (AF yes/no) is missing for a patient, the patient is excluded from the analysis (list-wise deletion). We use multiple imputation to obtain complete datasets and to see whether the original analysis is influenced by these missing data: i.e. to see whether the difference in detection rates between intervention and control groups is similar for both the original analysis (list-wise deletion) and the multiple imputation analysis.Diagnostic test characteristics of the different index tests to diagnose AF are compared with the results of the 12-lead ECG and 2-weeks Holter (composite reference standard). Sensitivity and specificity of each technique are calculated (including the corresponding 95 % confidence intervals). Because not all patients receive the reference standard, diagnostic parameters are estimated by converting studied numbers (i.e. results of test and reference standard) to the source population by multiplying them with the sample factor. For this, we use inversed probability weighting [31]. In the intervention group, we expect an incidence of AF of 2–3 %. This would result in sufficient numbers in all cells of the imaginary diagnostic 2x2 tables. We compare the diagnostic characteristics of the index tests to each other. We evaluate each method separately and in different combinations.

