**Methods/Design:**

In a multicenter cluster randomised controlled trial, we compare an enhanced protocol for case-finding of atrial fibrillation with usual care. We recruit 96 practices. We include primary care patients aged 65 years or older not diagnosed with atrial fibrillation. Within each practice, a cluster of 200 patients is randomly selected and marked. Practices are evenly randomised to intervention or control group. The allocation is not blinded.

When a marked patient visits an intervention practice, the case-finding protocol starts, consisting of: pulse palpation, sphygmomanometer with automated atrial fibrillation detection and handheld single-lead electrocardiogram (ECG). All patients with at least 1 positive test and a random sample of patients with negative tests receive a 12-lead ECG. Patients without atrial fibrillation on the 12-lead ECG, undergo additional continuous Holter and use the handheld single-lead ECG at home for 2 weeks.

Control practices provide care as usual.

The study runs for 1 year in each cluster. The primary outcomes are the difference in detection rate of new AF between intervention and control practices and the accuracy of three index tests to diagnose AF. We are currently recruiting practices.

The ‘Detecting and Diagnosing Atrial Fibrillation’ (D_2_AF) study will determine the yield of an intensive case-finding strategy and the diagnostic accuracy of three index tests to diagnose atrial fibrillation in a primary care setting.

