To detect cases of pAF, ambulatory rhythm recording is needed [19]. Traditionally, either 24-hour Holter or event recording is used. In post-stroke patients, a 30-day period of automatically triggered event recording increased the detection rate of pAF 5-fold compared with a 24-hour Holter (detection rate of 16.1 % versus 3.2 %) [20]. In primary care patients with palpitations, monitoring for 14 days diagnosed about 80 % of relevant arrhythmias [19].

New developments have enabled the use of continuous ECG registrations for longer periods (continuous Holter) and make loop recording unnecessary. In general, ambulatory rhythm recording is used in symptomatic patients or as part of follow-up after stroke. There is insufficient evidence about the effectiveness of ambulatory rhythm registration for the detection of AF in asymptomatic patients (in general practice). This is a major evidence gap and further research is recommended [21, 22].

The ‘Detecting and Diagnosing Atrial Fibrillation’ (D_2_AF) study investigates whether enhanced opportunistic case-finding – using pulse palpation, single-lead handheld ECG and eBPM-AF – increases detection of AF in general practice patients of 65 years and over. Additionally, the study determines the most effective method of case-finding by comparing the diagnostic yield of pulse palpitation, handheld ECG and eBPM-AF alone and in combination.

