All patients scoring positive on at least 1 of the 3 index tests will receive a 12-lead ECG in the same session as the index tests. To calculate sensitivity and specificity of the screening procedure, a random sample of 10 % of patients who score negative on all 3 index tests also receive a 12-lead ECG. An overview of these procedures can also be seen in Fig. 1. The sub-investigator is blinded to the ECG results while performing the index tests.

12-lead ECG: the 12-lead ECG device (Fysiologic®, Amsterdam, The Netherlands) is paperless and does not display the ECG. The ECG is transferred digitally and assessed by an experienced assessor, supervised by a cardiologist. In case the ECG shows any serious clinically relevant abnormality, the general practitioner (GP) is notified immediately. A second cardiologist re-assesses all AF-diagnosed ECGs and a random sample of negative ECGs. Both cardiologists are provided with basic data such as age and gender but are blinded to all previous measurements. Any disagreement on diagnosis is solved by a third cardiologist. AF is defined as the absence of distinct P waves and a completely irregular RR interval [24].

If a patient is diagnosed with AF, the study protocol is finished. Results of the ECG are reported back to the GP, who provides care at his discretion.

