In patients in whom no AF is diagnosed on a 12-lead ECG, 2 additional tests are performed to detect pAF:Handheld ECG at home: the same device (MyDiagnostick, ABS, Maastricht, The Netherlands) as mentioned above is used, but the indication light is set off. Thus, the patient is blinded for the results of the test (light will not blink). The patient is instructed to use the handheld ECG three times a day at set times. After 2 weeks of recording, data are uploaded as PDF in the local PC-application. The MyDiagnostick can store up to 140 ECG strips.Two-week Holter: the same device (Fysiologic®, Amsterdam, The Netherlands) as for the 12-lead ECG is used. The wiring has four different patches instead of ten. With these 4 patches, leads V1 and V5 are obtained. The patient receives a small disposable shoulder bag to wear the device and several sets of patches with instructions so they can change them. After 2 weeks of continuous recording, data are transferred and assessed by an experienced assessor, supervised by a cardiologist. The number and duration of AF episodes are registered. In case the ECG shows any serious clinically relevant abnormalities, the GP is notified immediately. A second cardiologist, blinded to previous assessments re-assesses all AF-diagnosed Holters. Furthermore, a random sample of negative Holters is re-assessed. We define AF as any arrhythmia that has the characteristics of AF (see above) and lasts at least 30 seconds [24].

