Besides the actual prevalence in the patient group, the efforts the doctors made to detect AF in the past determines the registered prevalence of AF in each cluster. Therefore, we expect the registered prevalence of AF in each practice to correlate negatively with the chance of detecting new AF. We will use prevalence of AF in patients aged 65 years and older as our stratification variable to equalise the chance of finding new AF in the intervention and control practices.

We use a case-finding protocol, which means that only patients making an appointment for a consultation are asked to participate. We preferred this method to systematic screening, where all patients are asked to participate. One of the reasons is that Hobbs et al. showed case-finding to be as effective as systematic screening [15].

In the intervention arm, we run a diagnostic study to determine the test characteristics of different case-finding methods for AF. Ideally, one should perform the reference standard in all patients. We considered this as too costly, time-consuming and interruptive for both patients and practices. Therefore, we decided to perform the composite reference test only in patients with a positive case-finding test and a small random group of patients with negative tests.

AF is an important risk factor for stroke, and early detection is desirable to enable prevention of serious complications. The D_2_AF study will provide valuable evidence on the efficacy of case-finding and on the best methods for detecting AF.

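### AF found only by the 10% verification sample of test-negative patients counts towards the primary yield in the intervention arm alone, which biases the yield of the case-finding strategy modestly upward

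*Protocol article*

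**What the plan says.** All references are to the protocol article.

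- **Question.** The Background asks whether opportunistic case-finding with pulse palpation, single-lead handheld ECG and eBPM-AF "increases detection of AF in general practice patients of 65 years and over". The abstract (Methods/Design) says that when a marked patient attends, "the case-finding protocol starts, consisting of: pulse palpation, sphygmomanometer with automated atrial fibrillation detection and handheld single-lead electrocardiogram (ECG").
- **Verification sample.** Under Diagnostic tests, every patient positive on at least one index test gets a 12-lead ECG. In addition, "a random sample of 10 % of patients who score negative on all 3 index tests also receive a 12-lead ECG". The purpose given is "To calculate sensitivity and specificity of the screening procedure".
- **Holter.** The same section continues: "In patients in whom no AF is diagnosed on a 12-lead ECG, 2 additional tests are performed to detect pAF". This is not limited to index-positive patients. The Discussion confirms that the composite reference test is done "only in patients with a positive case-finding test and a small random group of patients with negative tests".
- **Primary outcome.** Under Primary study outcomes the detection rate is "new cases of AF after 1 year within the clusters/all patients in the clusters". No route of detection is excluded. Inverse probability weighting is planned there for the accuracy parameters only.
- **Ascertainment.** Records are searched for all new AF. In intervention practices, the route to diagnosis is asked only for cases the intervention did not detect. Control practices give usual care and have no ECG or Holter sampling.

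**The concern.** Under the described strategy, a patient negative on all three index tests has no further work-up. The ECG and Holter in a random tenth of these patients are research verification, done so that sensitivity and specificity can be estimated without testing everyone. The primary numerator nevertheless counts any AF they reveal, and only one arm has this extra source of cases.

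The primary difference therefore estimates the yield of case-finding plus ECG and Holter in a random tenth of test-negative attenders, which is not a strategy the article proposes for practice. The distortion favours the intervention, and a larger sample does not reduce it. At stake are the headline difference in yield and, to a lesser degree, the type I error of its test.

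**Working it through.** **1. The plan's own figures reproduce.** A control rate of 1.3% and an OR of 1.8 give odds 1.8 × 0.013/0.987 = 0.02371, so a rate of 2.316% (stated: 2.32%). Two-sided 5%, 80% power, pooled variance and no continuity correction give 2699 per group (2681 if 2.32% is entered), against 2701 stated. Design effect: 1 + 199 × 0.01 = 2.99. Then 2701 × 2.99 = 8076, 8076/0.85 = 9501, and 48 × 200 = 9600 per arm. The point concerns what the outcome counts, not this arithmetic.

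**2. Formula.** Gross extra cases = 9600 × (share tested) × (share triple-negative) × 0.10 × (AF proportion on ECG or Holter in triple-negatives).

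From the article: 9600 and 0.10. Not in the article, so assumed: 40-70% tested, 85-90% triple-negative, 1-3% AF, and full uptake of ECG and Holter by those sampled.

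**3. Range.**
- Patients verified: 9600 × 0.40 × 0.85 × 0.10 = 326, to 9600 × 0.70 × 0.90 × 0.10 = 605.
- Extra cases: 326 × 0.01 = 3.3, to 605 × 0.03 = 18.1.
- In points: 3.3/9600 = 0.034%, to 18.1/9600 = 0.189%.
- Share of the target: 0.034/1.02 = 3%, to 0.189/1.02 = 19%.

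**4. Middle scenario.** With 50% tested and 85% triple-negative, 408 are verified.

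| AF in triple-negatives | Extra cases | Points | Share of 1.02 | Apparent OR if the index tests add nothing |
|---|---|---|---|---|
| 1.4% (single-time-point figure in the Discussion) | 5.7 | 0.06 | 6% | 1.05 |
| 3% (assumed) | 12.2 | 0.13 | 12-13% | 1.10 |
| 7.4% (upper bound only) | 30.2 | 0.31 | 31% | 1.25 |

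**5. Against the standard error.** SE = √{[0.013 × 0.987 + 0.0232 × 0.9768]/n × design effect}. The article gives two ICCs: 0.01 (design effect 2.99) and 0.0027 (1 + 199 × 0.0027 = 1.54).

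| n per arm | SE, ICC 0.0027 | SE, ICC 0.01 |
|---|---|---|
| 9600 | 0.24 points | 0.33 points |
| 9600 × 0.85 = 8160 (planned 15% loss) | 0.26 points | 0.36 points |

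At 1-3% AF the bias runs from 0.034/0.36 = 0.1 SE to 0.189/0.24 = 0.8 SE.

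**6. Effect on the test.** If the index-test strategy added nothing, the middle scenario with 9600 per arm would give a two-sided rejection rate of about 5.5-6% (1.4% AF) or 7-9% (3% AF), instead of 5%.

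**7. Why the weighting works.** In the middle scenario there are 9600 × 0.50 × 0.85 = 4080 triple-negatives: 408 sampled and 3672 not. Dropping the 408 and weighting the rest gives 3672/0.9 = 4080, so the denominator is restored. Because sampling is random, the unsampled patients show the AF that usual care alone would have found in all 4080 during the year.

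All the excess figures are gross. Usual care would have found some of these patients within the year, so the net excess is somewhat smaller.

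**The case against.** **The random check belongs to the delivered procedure.** The abstract describes the ECG in positives and in sampled negatives in one sentence, analysis is by intention to screen, and for the effect of the whole trial procedure the estimate is unbiased. That last statement is true, but it answers a different question from the one in the Background. ECG and Holter after a positive index test are the natural continuation of the strategy; a random check of negatives, given only an accuracy purpose, is not. Intention to screen settles who is analysed, not which tests count as the strategy.

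**The cases are not hidden.** They must be tabulated for the accuracy analysis, and an SAP may report them by route. This stands in part: the contribution can be counted afterwards. But the article states an all-cases numerator for the primary outcome, so this is not a detail left open.

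**The size is uncertain and probably modest.** This stands. A reader might infer a bias of one to two standard errors from the 7.4% quoted in the Discussion, which would give 24-45 cases, 0.25-0.47 points, or 25-46% of the target. The documents do not support that as an expectation. The 7.4% comes from systematic screening of 75-year-olds, not from patients aged 65 and over who have just tested negative three times. Even with 7.4%, nearly 2 SE (0.47/0.24) needs the highest attendance, the highest negative share, the lower ICC and no loss to follow-up together.

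**Recoding the cases as non-events would itself be biased.** This also stands. Usual care would have diagnosed some of them within the year, and the matching control patients would still count.

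**Conclusion.** The point holds in mechanism and direction: verification-only AF enters the primary numerator in the intervention arm alone and raises the apparent yield of the described case-finding strategy. The likely size is modest: about 0.03-0.19 points gross, or 3-19% of the planned 1.02 points and below one standard error. That range rests on assumed attendance, triple-negative share, AF proportion and full uptake, none of which the article gives; 7.4% is an upper bound.

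A reader might also infer that the verification sample could by itself make the trial positive. The figures do not support that: in the middle scenario at 1.4-3% AF, the apparent OR under no effect is only 1.05-1.10, against a planned 1.8.

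Should-fix; a cheap improvement.

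**What to change.** Pre-specify an estimate of the primary difference that drops the triple-negatives selected for verification and weights the unselected triple-negatives by 1/0.9. Drop by selection, whether or not the patient completed the ECG and Holter, so that randomness is preserved. All other patients keep weight 1. Base the conclusion about the case-finding strategy on this estimate, report AF found only through verification as a separate count, and show the all-cases result alongside. Do not recode verification-found AF as a non-event.

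**Cost.** No new testing. The index results are recorded in the eCRF. The article does not say that a sampling flag is stored there, but sampling status is needed anyway for the planned inverse probability weighting. The practice-level model must carry the weights. The headline difference becomes slightly smaller, with a small loss of precision from weighting.

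If the planned 2.32% was meant to include verification-found cases, which the article does not say, the middle scenario at 3% AF leaves 2.32 − 0.13 = 2.19% against 1.3%. Power at the planning ICC of 0.01, with 8160/2.99 = 2729 effective patients per arm, would then be about 71% instead of 81%.

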### Participants: practices and patients

General practices are recruited across The Netherlands. We regard two or more general practices sharing facilities as one practice. Within each practice, we form one cluster by selecting a random fixed sample of two hundred patients out of the eligible patients.

The inclusion criterion for selection of the cohort is an age of 65 years and over; the exclusion criterion is previously documented AF. Additional criteria are applied only to patients in the intervention group for whom case-finding would be inappropriate (see intervention practices). After selection of the study cohort, we extract the medical files to determine the baseline characteristics (e.g. age, sex and medical history including heart disease, hypertension, previous stroke/transient ischaemic attack (TIA), diabetes).

All data are entered into our secured trial management system. This system also gathers all other data during the study. Investigators enter data directly into the system using electronic case record forms (eCRF).

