### Cluster randomisation

Clusters are evenly allocated to either the intervention or the control group using stratified randomisation. To stratify clusters, we determine the prevalence of AF in all patients aged 65 years and over in participating clusters using International Classification of Primary Care (ICPC)-codes in the medical files. Subsequently, we stratify clusters in high-prevalence and low-prevalence clusters. As a cut-off we use the average prevalence of AF in the associated general practices of the 2 universities involved in this study: 8.05 %. We use computerised randomisation in permuted blocks of random sizes. After randomisation, the investigator informs the participating practices of the allocation.

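### The primary mixed model names no baseline covariate, although age, sex and cardiovascular history are extracted for the whole cohort; adjusting would bring a modest gain at almost no cost

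*Protocol article*

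**What the plan says.** In the protocol article, the section Primary study outcomes gives the model for the yield comparison in one sentence: "We use logistic mixed-effects models with practice as random factor for statistical analysis", with within-practice correlation as the reason. No patient-level covariate is named. Patients with a missing outcome are dropped, and multiple imputation is planned as a check on that.

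The section on participants (practices and patients) says that, once the cohort is selected, the medical files are extracted for baseline data, for example "age, sex and medical history including heart disease, hypertension, previous stroke/transient ischaemic attack (TIA), diabetes". Nothing there limits the extraction to one arm. Both the Background and the Discussion say that AF prevalence rises with age.

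The only balancing factor is registered AF prevalence in patients aged 65 and over: "we stratify clusters in high-prevalence and low-prevalence clusters", cut at 8.05% (section Cluster randomisation). The Discussion adds that, besides actual prevalence, "the efforts the doctors made to detect AF in the past determines the registered prevalence of AF in each cluster", and that "we expect the registered prevalence of AF in each practice to correlate negatively with the chance of detecting new AF".

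Two statements bear on whether patient-level adjustment is possible in the control arm. The section Statistical analysis says that outcomes are evaluated at patient level. The section Intervention practices explains the absence of consent in the control arm by saying that those patients are analysed only on a group level.

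**The concern.** The trial collects variables that, on the article's own account of age, should predict the outcome, and the stated model does not name them. Practices will differ in age and illness. That case-mix adds to the variation between practices, and any chance difference between arms stays in the estimated effect. The stratifier is a two-level practice characteristic, so it can equalise patient case-mix only roughly.

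Missing data matter too. Dropping patients with a missing outcome from a model without covariates is safe only if, within arm and practice, missingness is unrelated to age or illness. Once those variables are in the model, missingness may depend on them. Some precision and some robustness are at stake; the validity of the comparison is not.

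**Working it through.** **Inputs from the section Sample size calculation.** Control rate 1.3%, OR 1.8, intervention rate 2.32%, power 80%, significance level 5%, 200 patients per cluster, ICC 0.01 (0.0027 in the comparable study), 15% loss, 48 clusters per arm.

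**The plan's own figures.** Two proportions, two-sided 5%, no continuity correction: 2681 per arm with 2.32%, or 2699 with the unrounded rate of 2.316%, against 2701 stated. Design effect: 1 + 199 × 0.01 = 2.99. Then 2701 × 2.99 = 8076, and 8076/0.85 ≈ 9501. All reproduce, and none depends on covariate adjustment.

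**Where a gain can come from.** At event rates of 1.3–2.3%, adjusting a logistic model for patient-level predictors hardly changes the standard error of the log odds ratio. A gain comes from explaining variation between practices.

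**Assumptions (not in the documents).** Odds of AF rise 6–10% per year of age; practice mean age has an SD of 1–2 years; the overall rate is 1.8%; 170 patients per practice are analysed (200 less 15%).

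1. Between-practice variance due to age, logit scale: (ln 1.06 × 1)² = 0.0034 up to (ln 1.10 × 2)² = 0.0363.
2. Total between-practice variance, logit scale: approximately ICC / [p(1 − p)], with p(1 − p) = 0.018 × 0.982 = 0.0177. ICC 0.01 gives 0.566 (SD 0.75); ICC 0.0027 gives 0.153 (SD 0.39).
3. Share f explained by age: 0.6–6.4% at ICC 0.01; 2.2–23.8% at ICC 0.0027.
4. Gain in effective sample size = design effect before / design effect after, where the design effect after is 1 + 169 × ICC × (1 − f).

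| ICC | Design effect before | Design effect after | Gain | Power before | Power after |
|---|---|---|---|---|---|
| 0.01 | 2.690 | 2.680 to 2.582 | 0.4–4.2% | 84.6% | 84.8–86.1% |
| 0.0027 | 1.456 | 1.446 to 1.348 | 0.7–8.1% | 98.2% | 98.2–98.8% |

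Power is for 1.3% against 2.32% with 48 practices per arm. With all 200 patients analysed, the upper ends are 4.5% (power 86.6% to 88.0%) and 9.1% (99.0% to 99.4%).

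**Larger shares.** The article gives no strength for sex or history. At ICC 0.01 and 170 per practice, power would be 86.8% if all covariates together explained 10% of between-practice variance, 90.1% at 25% and 94.9% at 50%. Nothing in the article supports shares as high as the last two.

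**Simulation check.** 96 practices of 170, one covariate with log odds ratio 0.5–0.8 per SD, 2–10% of its variance between practices, 300 runs per scenario, logistic regression with practice-robust standard errors as a stand-in for the mixed model. The standard error fell by between 0 (0.207 to 0.207) and about 4% (0.157 to 0.150). Power changed by about −1 to +2 points, and each power estimate has a simulation error of about 2 points.

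**Chance imbalance.** The SD of the difference between arms in mean age is √(2/48) × (1 to 2 years) = 0.20 to 0.41 years. At the 95% limit (× 1.96) the difference is 0.40 to 0.80 years. Multiplied by ln 1.06 and ln 1.10, this moves the log odds ratio by 0.023 to 0.076, or 4–13% of ln 1.8 = 0.588.

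**The case against.** The strongest objection is that the article is a condensed account. The sentence on the model does not list the fixed effects at all; it does not even name the arm term, which must be there. A covariate list is often left to a full protocol or analysis plan. This stands in part: a reader might infer that the plan excludes covariates, and the article does not say so. It names none. What remains is a recommended change to the model as stated.

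Second, randomising 48 practices per arm keeps the unadjusted comparison valid, and no stated figure changes. This stands fully. A reader might infer bias or an error in the primary result, and there is no ground for either.

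Third, the gain is small. This also stands. A reader might infer that much power is being given up. Larger gains appear only with a smaller effect than the planned OR of 1.8, or with covariates that explain a large part of the between-practice variance. The article supports neither.

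Fourth, one might read the Discussion as saying that the stratifier mixes age structure with detection effort, and that the two act in opposite directions. It does not. It names actual prevalence and past detection effort, expects a net negative correlation with new AF, and does not mention age structure in that context.

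Fifth, baseline variables can enter the imputation model without being in the analysis model. That is true. But when only the outcome is missing and imputation uses no more than the analysis model does, imputation essentially reproduces the result of deletion. The planned check therefore needs baseline variables somewhere.

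Finally, the group-level wording might suggest that patient-level covariates are unavailable for control patients. That wording explains the lack of consent, while other sections describe patient-level evaluation and study of control patients' files (section Control practices). The statements need reconciling, but they do not show that the data are out of reach.

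**Conclusion.** The point holds as a modest gain in efficiency and robustness. The stated primary model names no baseline covariate although relevant ones are extracted for the cohort. The size given for the gain is for age alone and depends on the assumed age gradient, the spread of practice mean age and the ICC, so it should be read as a range. Sex and history could add to it by an amount the article does not allow one to calculate. Protection against chance imbalance and a weaker missing-data assumption are reasons of similar weight to the precision gain.

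**What to change.** Before outcome data are examined, pre-specify a short set of fixed effects in the primary logistic mixed model: age (continuous), sex, and cardiovascular history such as heart disease, hypertension, prior stroke/TIA and diabetes. Use the same variables in the multiple imputation model. Adjusted deletion and imputation should then nearly agree, so the informative contrast is with the unadjusted result.

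Adjustment makes the odds ratio conditional on the covariates. Report the difference in detection rate by standardising predicted probabilities over the cohort, which keeps the planned estimand. Keep the model without covariates as a supporting analysis.

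Reconcile the group-level description of control patients with the patient-level analysis, and state that their extracted baseline data may be used in the model.

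The cost is one or two sentences in the analysis section and one clarification. The plan already extracts these variables, so no new data collection and no change to the sample size are needed.

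### Accuracy data are weighted only for sampling, although only ECG-negative patients need a 2-week Holter to be verified; missing Holters would be expected to overstate sensitivity

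*Protocol article*

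**What the plan says.** All places are in the protocol article.

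- **Who is sent to the reference standard (Diagnostic tests).** Every patient with at least one positive index test "will receive a 12-lead ECG in the same session as the index tests". In addition, a random 10 % "of patients who score negative on all 3 index tests also receive a 12-lead ECG".
- **When verification ends (Diagnostic tests).** After the 12-lead ECG, "If a patient is diagnosed with AF, the study protocol is finished". Otherwise the work-up goes on: "In patients in whom no AF is diagnosed on a 12-lead ECG, 2 additional tests are performed to detect pAF". One of the two is the Holter, for which patients change the patches themselves: "After 2 weeks of continuous recording, data are transferred and assessed by an experienced assessor, supervised by a cardiologist".
- **What counts as AF.** The reference is a composite of the 12-lead ECG and the 2-week Holter.
- **How accuracy is estimated (Primary study outcomes).** The reason given for weighting is that only some patients undergo the reference standard. The method is described as "converting studied numbers (i.e. results of test and reference standard) to the source population by multiplying them with the sample factor", and inverse probability weighting is named for it with a methods reference.
- **Missing outcomes (same section).** List-wise deletion and multiple imputation are described for the yield comparison, and the imputation is there to check the between-arm difference in detection rates. Nothing is stated for an ECG-negative patient whose Holter is absent or incomplete.

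**The concern.** The sample factor follows from the design: 1 for any-positive patients and 10 for triple-negative patients, as inferred from the sampling fractions. It restores the source population if everyone selected for the reference standard completes it. Here, completion depends on the first component of the reference itself. A patient with AF on the ECG is verified within minutes. A patient without it is verified only after two weeks of wearing a recorder. A weight that depends only on index-test results cannot remove a dependence on the ECG result.

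Lost Holters remove only AF that the ECG did not show. The index tests are done at a single visit, and the Discussion concedes that a pulse check or ECG on a single occasion can fail to pick up paroxysmal AF. Holter-only AF should therefore contain a larger share of false negatives. Losing it makes the tests look better than they are, on one of the two primary outcomes.

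**Working it through.** **Figures in the plan.** None is stated for Holter completion or for the precision of the accuracy estimates. The 15 % loss to follow-up belongs to the yield sample size (2701 × 2.99 = 8076; 8076 / 0.85 = 9501). The inputs below are therefore assumptions, apart from total AF, which is kept within the 2–3 % that the plan expects in the intervention group.

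**Set-up.** Let E be the percentage of patients with AF on the ECG and P the percentage with AF only on Holter. Let s_E and s_P be the index sensitivity in each, and c the Holter completion among ECG-negative patients. After multiplication by the sample factor, the expected table has source-population proportions, so the factor of 10 cancels and only completion remains:

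estimated sensitivity = (E·s_E + c·P·s_P) / (E + c·P); the true value has c = 1.

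**Worked case.** E = 1.4, P = 1.0, s_E = 0.95, s_P = 0.20.

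- True: (1.33 + 0.20) / 2.40 = 0.637 (0.6375 unrounded)
- c = 0.85: (1.33 + 0.17) / 2.25 = 0.667
- c = 0.70: (1.33 + 0.14) / 2.10 = 0.700
- c = 0.50: (1.33 + 0.10) / 1.90 = 0.753

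**Range of assumptions** (s_E = 0.95 throughout):

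| E % | P % | s_P | true | c = 0.85 | c = 0.70 | c = 0.50 |
|---|---|---|---|---|---|---|
| 1.4 | 1.0 | 0.20 | 0.637 | 0.667 | 0.700 | 0.753 |
| 1.4 | 1.0 | 0.40 | 0.721 | 0.742 | 0.767 | 0.805 |
| 1.2 | 1.2 | 0.20 | 0.575 | 0.605 | 0.641 | 0.700 |
| 1.2 | 1.2 | 0.40 | 0.675 | 0.697 | 0.724 | 0.767 |
| 1.0 | 2.0 | 0.20 | 0.450 | 0.478 | 0.512 | 0.575 |
| 1.0 | 2.0 | 0.40 | 0.583 | 0.604 | 0.629 | 0.675 |

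The bias is about +2 to +3 points at 85 %, +5 to +7 at 70 % and +8 to +13 at 50 %.

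**Does another reading of the plan remove it?**

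- *Incomplete Holter counted as no AF.* True positives and false negatives are the same as under deletion, so sensitivity is identical.
- *Sample factor read as the realised verified fraction per index stratum.* In the worked case at 85 %, with an assumed specificity of 0.85, the result is 0.663 against 0.637. The bias remains.

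**When does the sign change?** With completion a in index-positive and b in index-negative patients, the worked case gives (1.33 + 0.20a) / (1.33 + 0.20a + 0.07 + 0.80b).

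- a = 0.90, b = 0.70: 1.51 / 2.14 = 0.706, a larger bias
- a = 0.50, b = 0.95: 1.43 / 2.26 = 0.633, slightly below the true value
- with s_P = 0.40, a = 0.70, b = 0.95: 1.61 / 2.25 = 0.716 against a true 0.721

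If s_E = s_P and completion is equal, there is no bias. Specificity is unaffected when a = b.

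**Check of the fix.** Dividing the ECG-negative contributions by c = 0.85 (weights 10 / 0.85 = 11.8 and 1 / 0.85 = 1.18, with ECG-positive patients left at 10 or 1) turns 0.17 back into 0.20 and 0.85 back into 1.00. The result is 1.53 / 2.40 = 0.637, if non-completion is random within index strata.

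**The case against.** **Level of detail.** Sampling weights are the right correction for the partial verification that the plan intends, and an article may leave rules for incomplete recordings to a fuller document. This stands for the details of a minimum recording time. It does not dispose of the point, because the article does state the estimator for a primary outcome, and that estimator as written does not address Holter completion. The cited weighting reference cannot be consulted here, so a broader weight cannot be ruled out.

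**Size.** The table treats all AF in an incomplete Holter as lost, yet AF needs only a 30-second episode. If half of the AF cases with an incomplete Holter show AF before recording stops (an assumption), 70 % completion loses 15 % of Holter AF and the estimate is 0.667, not 0.700. This stands.

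**Sampling error.** It may be larger. With assumed weighted counts of 80 true positives and 45 false negatives, sensitivity is 80/125 = 64.0 %. The 45 represent about 4.5 real triple-negative patients. One more or one fewer gives 80/135 = 59.3 % or 80/115 = 69.6 %. This also stands, but a systematic error does not shrink with more patients and is not reflected in the confidence interval.

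**Inferences that the document does not support.**

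- That a negative Holter of a few days is accepted as equal to a full one. The article says nothing of the kind; it describes assessment after two weeks.
- That the Background figure, "a 30-day period of automatically triggered event recording increased the detection rate of pAF 5-fold compared with a 24-hour Holter", measures the loss from a short Holter. It compares different devices in post-stroke patients and cannot be carried over to shorter against longer wear of one recorder in primary care.

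**Conclusion.** The point holds as an expected bias. With any Holter non-completion, weighting by the sample factor alone is expected to overstate the sensitivity of the index tests and their combinations. Two conditions are needed. Index sensitivity must be lower for Holter-only AF, which the Discussion makes plausible. Index-positive patients must also not complete Holters clearly less often than triple-negative patients.

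A reader might infer that sensitivity will certainly be inflated, or inflated by a known amount. The document supports neither: the sign can reverse slightly if the second condition fails, and neither Holter completion nor the split between ECG-detected and Holter-only AF is given. The ranges of +2 to +3 points at 85 % and +5 to +7 at 70 % rest entirely on assumed inputs and shrink if incomplete Holters still reveal AF. The yield comparison is not touched by this point.

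**What to change.** In Primary study outcomes:

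1. For ECG-negative patients, multiply the sampling weight by the inverse of the estimated probability of an adequate Holter, modelled on index-test pattern and collected covariates such as age, sex and symptoms. ECG-positive patients keep a second factor of 1.
2. Define an adequate Holter in advance by analysable recording time alone, whatever it shows. In the accuracy analysis, short Holters with and without AF are then both unverified; AF found on a short Holter still counts for yield. Accepting short Holters only when they show AF would make verification depend on the result again. In the worked case at 70 % completion, with half of the remaining AF still seen, the Holter AF would be multiplied by 0.85 / 0.70 = 1.214. The estimate would be (1.33 + 0.243) / (1.40 + 1.214) = 0.602 against a true 0.637.
3. Add bounds that set all unverified patients to AF and then to no AF. The first will be wide: 15 % of the 98.6 % who are ECG-negative is 14.8 % of patients, against 2.4 % with AF.

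**Cost.** One extra model, export of analysable Holter time, and wider confidence intervals, because a few triple-negative AF cases carry larger weights (10 / 0.70 = 14.3 at 70 % completion). The correction also assumes that, given the modelled variables, Holter completion among ECG-negative patients is unrelated to AF.
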